**Enrollment**

Patients arriving at the clinic will provide their health card or name to a clinic staff member, who will check the list of possible study participants for his/her name. If the patient’s name is on the list, the clinic staff member will ask the patient if he/she is interested in hearing about the project. If the patient is interested in hearing about the project, the clinic staff member will introduce the patient to a research study project interviewer or project coordinator. Each interested patient will be taken to a quiet place in the waiting area outside of hearing range of other patients and staff or, if possible, to a private room. They will be told about the project and asked screening questions (Appendix C) to assess project eligibility. Patients who are eligible will be asked to participate in the project but will be assured that their decision about participation will not affect the care they receive in the clinic. Those who decline will be thanked for their time. Those who agree to participate in the project will complete the project consent process (described in the next section) and complete the baseline interview. If the participant is not available at the time of enrollment to complete the interview, he/she will be scheduled to return to the HIV clinic within 10 days to meet with a project interviewer.

**Consent process**

Eligible persons choosing to participate will be shown the consent form (Appendix D). Printed consent forms will be available in the participant’s chosen language and will be read to the participant by the project interviewer in that language. Potential participants will be informed that their participation is voluntary, that they do not have to answer questions that make them uncomfortable, and that all information will be kept private (i.e., no personal identifiers will be used and only summary information across all participants will be reported). Although there are no anticipated risks for participating in the interviews, some individuals may experience emotional discomfort with the questions. If this should occur, participants will be reminded that they are free to withdraw their participation at any time or may refrain from answering any questions that make them uncomfortable. Patients will be informed that their participation or refusal to participate will not in any way affect their care or treatment. They will be invited to ask questions about any aspect of the project and their participation, and the interviewer will answer them. Participants will be informed that all information collected for this project is confidential and will not be shared with any hospital staff (aside from the project coordinator and interviewers) or their family, friends, or employers. If they agree to participate in the project, participants will sign their name on the consent form to indicate they have obtained the information and voluntarily agree to participate. Those who are not able to sign due to literacy issues will provide a thumbprint, as is customary in the participating countries.

Health care providers and lay counselors will have the option of participating in the evaluation of the project. That is, they will be able to choose whether to complete the questionnaires and allow observation of their interactions with patients/participants. The purpose and requirements of participating in the intervention evaluation will be explained and all questions will be answered. If interested in participating in the project, health care providers and lay counselors will read and sign the consent form. They will be informed that their participation is voluntary and that their jobs will not be affected by their participation in this project. They are free to withdraw at any time or refuse to answer any questions that make them uncomfortable. No information gathered from this evaluation will be shared with participants’ co-workers or supervisors.

There will be a master list with each participant’s name and an assigned identification number. That identification number will be written on all data collected; participant names will not appear on any data. Patients, health care providers, and lay counselors who enroll in this project will each be assigned an identification number so that their name is not linked to their questionnaires or data, in order to protect their confidentiality. Only the site project coordinator will have access to the master list so they can ensure that data across project visits can be linked correctly to each participant. The master list will be locked in a filing cabinet in a secure room in the clinic. At follow-up project visits, participants will tell the project coordinator their name, the coordinator will consult the master list for the identification number, and that number will be entered on all forms and in the database. All information collected (medical chart information and interviews) will be stored securely in the researchers’ offices or on computers with secure access. The CDC-Atlanta, ICAP-New York, and in-country research teams will only have access to the data without identifiers that can link to individual patients.

**PROCEDURES/METHODS: VARIABLES/INTERVENTIONS**

**Variables**

Variables will be collected from patients and from clinic charts. The variables will include both behavioral and biologic dependent variables. In addition, we will examine several potential variables that may mediate the hypothesized changes in outcome variables. The following paragraphs describe our primary outcome variables, our primary independent variables, and potential mediating variables.

Primary Outcome Variables

The primary outcome variables will be compared for those in the intervention and those in the comparison arms. These variables have been discussed previously and include self-reported sexual risk behaviors (e.g., any unprotected sex in the past 3 months, number of sex partners, proportion of sex acts that are unprotected with HIV-negative or unknown status partners), disclosure of HIV status to sex partners, partner testing for HIV, alcohol use, HIV medication adherence, STIs (i.e., urethral discharge) unintended pregnancies, family planning and safer pregnancy counseling, and family planning services (e.g., contraception).

Independent Variables

As discussed, we propose conducting a longitudinal cohort project with a two arm design. The intervention group will consist of participants from clinics in which the staff have been trained to provide the HIV prevention intervention package and the comparison group will be participants from clinics providing the current standard of care. For our primary outcomes, we will use an intent-to-treat (ITT) analysis approach. That is, participant data will be analyzed based on the project arm to which they were assigned. Thus, intervention or comparison arm will serve as our primary independent variable in these analyses.

The ITT approach preserves the unbiased comparability between the intervention arm and the comparison arm that results from random assignment, thereby strengthening our project’s internal validity. Furthermore, our primary research questions focus on hypothesized outcomes associated with providing a package of HIV prevention interventions for HIV-positive persons, and analyzing the data based on the project condition to which participants were randomized will allow us to examine the impact of this intervention.

In addition to our primary ITT analysis, we plan to examine other independent variables and their relationship to our outcome variables described above. These variables include number of clinic visits, amount of time spent with health care providers and lay counselors during clinic visits, and prevention activities discussed.

Potential Mediating Variables

Our potential mediating variables include domains such as physical and mental functioning, HIV transmission risk knowledge and perception of HIV transmission risk, social support, sexual self-efficacy, communication with partner, STI symptoms, CD4, and physical and sexual violence. Within each of these domains, our questionnaire will use sets of items to measure various subcategories of these domains. Scores on these items will be used as mediating variables to examine whether they impact our proposed primary outcome variables.

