**General Approach**

The general approach will be confirmatory (hypothesis testing). The project will use data collected from the baseline and follow-up measures to compare changes over time between persons at the clinics randomly assigned to receive the HIV prevention intervention package and persons who are at the comparison clinics receiving the standard of care for that country. Quantitative analyses will be conducted to examine the research questions outlined above and to test associated hypotheses.

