**Participant exclusion criteria**

Clinic patients

- Younger than 18 years of age
- Not sexually active within the last three months
- Planning to move from the vicinity of the clinic within one year
- Not enrolled in the HIV clinic and/or have not been seen for at least two clinic visits
- Cannot provide informed consent
- Patients who are acutely ill or are determined by clinical staff to be too ill to participate
- Spouses or identified partners of participating patients
- Pregnant women and male partners of pregnant women, as family planning counseling and unintended pregnancy are some of the primary study outcomes
- Not able to complete interview in one of the languages in the inclusion criteria
- Participated in pilot study

Health care providers and lay counselors

- Younger than 18 years of age
- Not fluent/literate in the language selected for the project training
- Planning to leave the clinic within one year
- Not willing to complete project questions
- Do not agree to be observed during patient visits

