**Sampling, including sample size and statistical power**

Participants will be sampled from the database of patients already receiving care at the project clinics. Information about gender, whether on ART, and last clinic visit will be used to create a list of potential participants. From that list, patients will be randomly selected to create a list of patients to approach about participating in the project. When patients arrive at the clinic the list will be checked and if their name is on it they will be asked if they are interested in participating in the project (see enrollment section below for further description). If they are not, their name will be removed from the list. Each clinic will enroll approximately half of each gender and half who are on ART. A tally of persons in each of the gender by ART cells will be kept updated daily. As each of the cells near the enrollment targets the study coordinator will monitor the potential participant list to ensure that appropriate numbers of participants are in each group.

The primary outcome variable for the project will be participant self-report of any unprotected sex in the past 3 months. Prior studies have found rates of condom use to be very low in the areas in which this project will be conducted (Arthur et al., 2007; Feldblum et al., 2000; Kapiga et al., 2006; Mwaluko et al., 2003; Norman, 2003; Stanton et al., 1999; Ross et al., 2007; Watson-Jones et al., 2007). We will assume a rate of at least 50% for any unprotected sex in the past 3 months in the comparison condition for sample size estimation.

Although the proposed project includes measurements at three time points (baseline, 6 months and 12 months), sample size estimates are presented for the simple difference between proportions in the two project conditions at the 12-month follow-up only. This approach is conservative because analytic approaches taking into account the multiple observations on each participant will be more powerful. We use the cross-sectional approach for sample size estimation because no prior data are available on which to base prediction of the pattern of intervention effects over time and the magnitude of the over-time correlation of groups and group members that we can expect in this project. Our sample size estimates do take into account expectations of attrition in the project cohort, which we expect to be moderate (at most 30% at the 12-month follow-up).

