In the following sample size table, we present calculations for the number of clinics needed for at least 80% power to detect differences of varying size between the intervention and comparison conditions with a two-sided test and α=0.05. Sample size estimates are based on a formula in Murray (1998) for group-randomized trials:

Where g is the number of groups per condition, and are the event rates in the two project conditions, *m* is the number of members per group (clinic), is the intraclass correlation coefficient measuring the correlation of members nested within groups, nested within project conditions, and and are critical values from the t-distribution.

Table 1 presents the sample sizes necessary for at least 80% power to detect a 20-30% reduction in the rate of unprotected sex in the past 3 months in the treatment condition compared to the comparison condition at the 12-month follow-up. We use 50% as the rate of unprotected sex in the comparison condition for sample size estimation; if the actual rate is higher or lower with the same reduction in the treatment condition, power will be greater, as variance in the binomial distribution is largest at 50% and decreases as the event rate moves away from 50% in either direction. Power calculations for group-randomized trials also need to take the expected intraclass correlation coefficient (ICC) into account to have adequate power. However, there are no prior published reports of ICCs for sexual risk behaviors among clinic attendees in sub-Saharan Africa on which to base our power calculations. A prior study did report an ICC of .0011 for STI prevalence at the community level in Kenya (Feldblum et al., 2000), and another study presented an ICC of about .01 for any unprotected sex in the past 90 days in a neighborhood-randomized trial in the U.S. (Pals et al., 2008). ICCs are generally larger for behavioral variables than for biologic variables and also generally increase as the group size decreases (e.g. larger for clinics than for communities). Murray and Blitstein (2003) showed that including multiple timepoints in analytic models can substantially reduce the ICC. Based on these prior results, we use ICCs of .01 and .02 for sample size estimation.

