**Table 1. Number of groups and members per condition needed for at least 80% power to detect a 20-30% difference between intervention and comparison conditions in report of any unprotected sex in the past 3 months (assuming intraclass correlations of 0.01 or 0.02).**

| **P1** | **P2** | | **ICC** | **Absolute Difference** | **% Difference** | **Members per group enrolled** | **Members per group retained** | **Number of groups needed per condition** |
| --- | --- | --- | --- | --- | --- | --- | --- | --- |
| .50 | .3875 | | .01 | .1125 | 22.5 | 200 | 140 | 7 |
| .50 | .3750 | | .01 | .1250 | 25 | 200 | 140 | 6 |
| .50 | .3625 | | .01 | .1375 | 27.5 | 200 | 140 | 5 |
| .50 | .3500 | | .01 | .1500 | 30 | 200 | 140 | 4 |
| .50 | | .3750 | .02 | .1250 | 25 | 200 | 140 | 9 |
| .50 | | .3625 | .02 | .1375 | 27.5 | 200 | 140 | 7 |
| .50 | | .3500 | .02 | .1500 | 30 | 200 | 140 | 6 |

P1=proportion reporting any unprotected sex in the comparison group; P2=proportion reporting any unprotected sex in the intervention group

Table 1 shows that with 9 clinics per condition, each with 200 patients enrolled, the project would have at least 80% power to detect a 25% difference between intervention and comparison (absolute difference of 12.5%) with an ICC of 0.02. If the ICC is smaller or the intervention effect larger, power will be greater then 80%.

Summary

We anticipate enrolling 200 patients per clinic with 9 clinics per condition (3 per condition per country), for a total of 18 clinics and approximately 3600 patients (at least 2520 retained at 12 months). Power calculations demonstrate that this number of participants will allow us at least 80% power to detect a 25% relative difference between conditions for the primary outcome variable of any unprotected sex during the past 3 months, allowing for up to 30% loss to follow-up.

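### The protocol names one primary outcome in the sample-size section but lists eleven in the Variables section, and the design is sized for only one

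*Protocol*

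**What the plan says.** **One primary outcome.** The Protocol section on sampling, sample size and statistical power states: "The primary outcome variable for the project will be participant self-report of any unprotected sex in the past 3 months". The summary closing that section, the section on outcomes and minimum meaningful differences, and the captions of Tables 3 and 4 in the Data analysis plan all keep the singular.

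**Several primary outcomes.** In the Variables section, the paragraph on primary outcome variables opens: "The primary outcome variables will be compared for those in the intervention and those in the comparison arms". It then names eleven:

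1. any unprotected sex in the past 3 months
2. number of sex partners
3. proportion of acts unprotected with HIV-negative or unknown-status partners
4. disclosure to partners
5. partner testing
6. alcohol use
7. medication adherence
8. STIs (urethral discharge)
9. unintended pregnancy
10. family planning and safer pregnancy counseling
11. family planning services

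The plural returns in the intent-to-treat commitment under Independent Variables and in the paragraph on mediating variables. The exclusion criteria say that "family planning counseling and unintended pregnancy are some of the primary study outcomes", and the section justifying exclusions repeats this as the reason for excluding pregnant women and male partners of pregnant women.

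**Status of the tests.** The Hypotheses section states nine hypotheses without ranking them, and the General Approach section calls the approach confirmatory. The word secondary is applied to analyses, such as that of intervention actually received, and never to an outcome.

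**The concern.** Which outcomes are primary decides what counts as the trial's result, and this protocol gives two incompatible answers. On the first, one test at 0.05 settles the question. On the second, a significant result on any of eleven variables could be reported as a result on a primary outcome, although the trial was sized for only one of them.

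The plural is hard to dismiss as a slip. It occurs in several sections, and in the eligibility text it is the stated justification for a design decision. An analysis plan that followed either answer would contradict part of the protocol.

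**Working it through.** **Inputs, all from the sample-size section**
- Test and power target: "at least 80% power to detect differences of varying size between the intervention and comparison conditions with a two-sided test and α=0.05".
- Comparison rate: "We use 50% as the rate of unprotected sex in the comparison condition for sample size estimation", so p1 = 0.50.
- Design effect size: "25% difference between intervention and comparison (absolute difference of 12.5%) with an ICC of 0.02", so p2 = 0.375 and d = 0.125.
- Intraclass correlation: "we use ICCs of .01 and .02 for sample size estimation".
- 9 clinics per condition, 200 enrolled and m = 140 retained per clinic.

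The formula itself did not survive in the text. I used the usual group-randomized form with df = 2(g − 1), which is an assumption:

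g = [p1(1−p1) + p2(1−p2)] × [1 + (m−1)ICC] × (t_α/2 + t_β)² / (m d²)

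**Step 1. Reproduce the plan's figure for one outcome at 0.05, ICC 0.02.**
- Variance sum: 0.25 + 0.234375 = 0.484375.
- Design effect: 1 + 139 × 0.02 = 3.78.
- Standard error at g = 9: √(0.484375 × 3.78 / (140 × 9)) = 0.0381.
- d/SE = 0.125/0.0381 = 3.28. The critical t on 16 df is 2.12.
- Power is about 86.8%. The smallest g that satisfies the formula is 8.

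Table 1 states 9 for this row, so the claim of at least 80% power holds with some margin. Over all seven rows the formula gives 7, 6, 5, 5, 8, 7, 6 against the stated 7, 6, 5, 4, 9, 7, 6. The row stating 4 has power of about 79%. None of this affects the present point.

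**Step 2. Error rate if all eleven variables are primary at 0.05 each.**
- Independent, all nulls true: 1 − 0.95^11 = 0.431.
- The protocol gives no correlations between outcomes. For equally correlated normal test statistics (assumed):

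| Assumed common correlation | Chance of at least one false positive |
|---|---|
| 0 | 43% |
| 0.3 | about 37% |
| 0.5 | about 30% |
| 0.8 | about 18% |

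**Step 3. Could the design carry eleven primaries?** As an illustration only, take a Bonferroni split, 0.05/11 = 0.00455, with the same effect and 9 clinics per condition. The critical t on 16 df becomes 3.30.

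| ICC | d/SE | Power at 0.05 | Power at 0.00455 | Clinics per condition for 80% at 0.00455 |
|---|---|---|---|---|
| 0.02 | 3.28 | 86.8% | 49% | 14 |
| 0.01 | 4.12 | 96.9% | 79% | 10 |

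The planned size fits one primary outcome at 0.05. It does not fit eleven with this split.

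**The case against.** The best defence is that the protocol does identify its primary outcome. The sample-size section makes unprotected sex primary for the project as a whole, and three other places repeat the singular. In the Variables section, primary may simply mean main, set against mediating variables. On that reading no adjustment across outcomes is needed. This carries weight: the text favours a single primary outcome, and a reader who inferred that the primary claim is undefined would go too far. It does not dispose of the eligibility text, which counts two further outcomes among the primary ones and rests an exclusion on that.

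Four other inferences are tempting and are not supported:

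- **That a missing multiplicity rule is itself a fault.** Such a rule is commonly placed in the statistical analysis plan, which is not at hand.
- **That all eleven variables are confirmatory hypotheses.** The Hypotheses section has nine. It has none for the proportion of unprotected acts with HIV-negative or unknown-status partners, and it joins family planning counseling and services in one clinic-level hypothesis. The list of eleven is also introduced as examples, so the count is of those named.
- **That readings at 6 and 12 months double the number of tests.** The Data analysis plan tests time by condition first and pools the two timepoints unless that term is significant.
- **That the primary outcome must be fixed at 12 months only.** Twelve months is the basis of the sample-size calculation, described there as a conservative simplification. The planned model uses both follow-up times.

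The 43% is also a ceiling. It requires independence, all nulls true, and a rule that any one significant outcome counts as success. No section states such a rule, and several outcomes overlap.

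**Conclusion.** The protocol contradicts itself on which outcomes are primary and should be corrected. Its sample size supports the single-outcome reading. If the list in the Variables section were followed as written, with each variable tested at 0.05, the chance of at least one false positive result on a primary outcome would be at most 43%, and about 18% to 37% for assumed equal correlations from 0.8 down to 0.3. These figures assume that all null hypotheses are true and that no adjustment is made. A reader might infer that the sample size is wrong; it is not, since power for the one stated primary outcome is above 80% under the protocol's own assumptions.

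**What to change.** 1. In the Variables section, state that any unprotected sex in the past 3 months is the sole primary outcome, tested by the mixed model in the Data analysis plan, with 6 and 12 months handled as that model already provides.
2. Retitle the list there as primary and secondary outcome variables, and label the other ten as secondary.
3. Match the wording in the exclusion criteria, the justification of exclusions and the paragraph on mediating variables. The exclusion itself stays as it is.
4. Word the intent-to-treat commitment to cover all outcomes, so that relabelling does not narrow it.
5. State, beside the Hypotheses or General Approach text, that p-values for secondary outcomes are non-confirmatory.

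The cost is wording in a handful of places, with no change to sample size, eligibility, data collection or the primary model. The one real downside is that secondary outcomes, including unintended pregnancy, can no longer support a confirmatory claim on their own.
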